## Abstract

**Background:**

Impairment of exercise capacity remains a common adverse effect of non-small cell lung cancer (NSCLC) survivors after surgery. Previous research has suggested that Tai Chi Chuan (TCC) offers an exercise capacity benefit in several types of cancers. This is a randomized trial to investigate the efficacy and safety of TCC in postoperative NSCLC patients over an observation period of 3 months and a 9-month follow-up.

**Methods/design:**

Using a prospective, one center and randomized design, 120 subjects with histologically confirmed stage I–IIIA NSCLC following complete surgical resection will potentially be eligible for this trial. Following baseline assessments, eligible participants will be randomly assigned to one of two conditions: (1) TCC training, or (2) placebo control. The training sessions for both groups will last 60 min and take place three times a week for 3 months. The sessions will be supervised with target intensity of 60–80% of work capacity, dyspnea, and heart rate management. The primary study endpoint is peak oxygen consumption (VO_2peak_), and the secondary endpoints include: 6-min walk distance (6MWD), health-related quality of life (HRQoL), lung function, immunity function, and the state of depression and anxiety. All endpoints will be assessed at the baseline and postintervention (3 months). A follow-up period of 9 months will be included. The main time points for the evaluation of clinical efficacy and safety will be months 3, 6, 9, and 12 after enrollment.

**Discussion:**

This study will assess the effect of group TCC in postsurgery NSCLC survivors on VO_2peak_, lung function, and other aspects. The results of this study will eventually provide clinical proof of the application of TCC as one kind of exercise training for patients across the entire NSCLC continuum, as well as information on the safety and feasibility of exercise.

**Trial Registration:**

Chinese Clinical Trial Registry: ChiCTR-IOR-15006548. Registered on 12 June 2015.

**Electronic supplementary material:**

The online version of this article (doi:10.1186/s13063-017-2320-x) contains supplementary material, which is available to authorized users.

## Background

Lung cancer is a prevalent issue worldwide. Data from 2011 indicated that lung cancer, comprising 18.6% of the total new cases and 13.6% of the total deaths, is the most frequently diagnosed cancer in males and the leading cause of cancer death for each sex in both economically developed and developing countries [1]. With a 5-year survival of 14%, it was estimated that about 159,260 Americans would die from lung cancer in 2014 [2]. Lung cancer is histologically categorized into small cell lung cancer (SCLC) and non-small cell lung cancer (NSCLC) (approximately 85% of those diagnosed with lung cancer), and the survival of patients with the latter is much higher than those diagnosed with SCLC [3].

Surgical removal remains the best curative option for patients with early-stage NSCLC and for appropriately selected patients with locally advanced disease. Approximately 26,000 individuals per year in the United States will survive more than 5 years after initial diagnosis of operable disease [4]. With the government’s focus on the early detection of lung cancer screening, an increasing number of patients with early-stage disease were detected, thus elevating the number of curable and surgical resection cases [5]. Despite the improvement in surgical techniques and the survival rate, surgery is still associated with significantly reduced exercise capacity, which in turn is associated with increased morbidity [6, 7] along with functional limitations, decreased health-related quality of life (HRQoL), and psychiatric issues [8].

Clinicians are paying more and more attention to improving overall physical and emotional function as well as longevity. A growing interest has arisen in the use of non-pharmacological interventions such as exercise, which has been identified as a safe and effective way to improve aerobic capacity, strength, body composition, and HRQoL, as well as to reduce fatigue, emotional distress, and lymphedema symptoms in diverse cancers [9–14]. To our knowledge, preliminary data suggest that exercise intervention compared with usual care is associated with improved exercise capacity for postsurgery patients [15]. Nevertheless, the results have been conflicting and the optimal program is still to be determined, such as the type of exercises [16].

Tai Chi Chuan (TCC) is a traditional Chinese exercise oriented in thousands of years of ancient history. It combines meditation with slow and gentle movements, as well as deep breathing to move vital qi throughout the body. It is considered as a complex, multicomponent intervention that involves physical, psychosocial, emotional, spiritual, and behavioral elements [17]. The results of a systematic review including 1868 participants suggested that TCC has a positive effect on the majority of outcomes of exercise capacity including peak oxygen consumption (VO_2peak_) [18]. Furthermore, a recent meta-analysis that pooled the effect of 12 controlled trials examining the efficacy of TCC to improve the cancer-specific HRQoL reported that the weighted mean difference was 7.99 (95% confidence interval (CI) 4.07–11.91; *Z* score = 4.00, *p* < 0.0001) [19]. In addition, compared with conventional exercises, research among 61,477 adults revealed TCC as the most common forms of exercise among Chinese adults and is related to reduced cancer-caused mortality [20]. Meanwhile, as a mind-body technique, TCC has been found to better lower mental disorder and fall rate in cancer survivors relative to conventional therapeutic exercise [21]. Given the clinical benefits of TCC, none of these studies evaluated the influence of TCC among postoperative NSCLC patients.

In light of this evidence, we designed a single-blind randomized controlled trial to evaluate the efficacy and feasibility of TCC on postoperative NSCLC patients. We hypothesize that TCC may serve as a safe exercise intervention that offers potential benefit among postsurgical NSCLC survivors.

## Methods

### General objective

To investigate the efficacy and feasibility of TCC on postoperative NSCLC patients with the aim of confirming the effectiveness and safety of TCC.

### Study design and procedures

The study will be a prospective, single blind, parallel group, randomized controlled trial. We will recruit and randomize 120 histologically confirmed stage I–IIIA postsurgical NSCLC patients 1:1 into two groups: 1) TCC training; or 2) placebo control. The study period will be 12 months including a 3-month supervised exercise training course and a 9-month follow-up course with the first and secondary outcomes measured at baseline, and at 3, 9, and 12 months, along with other assessments. The procedure is shown in Fig. 1. All patient visits, exercise, and assessment will take place in Guang’an men Hospital, China Academy of Chinese Medical Sciences, Beijing, China. This report will be compiled in line with the SPIRIT (Standard Protocol Items: Recommendations for Interventional Trials) 2013 Statement “Defining Standard Protocol Items for Clinical Trials” [22]. Additional file 1 shows this in more detail.

**Fig. 1 Fig1:**
[figure not shown]
Flow diagram. *TCC* Tai Chi Chuan

### Participants

This study will be conducted in the Department of Oncology, Guang’an men Hospital, China Academy of Chinese Medical Sciences. Each member of staff of the study team will be able to enroll participants. Inclusion criteria will be as follows: 1) histologically diagnosed with Stage I–IIIA NSCLC according to the 7th edition cancer staging manual of the American Joint Committee on Cancer [23] and had received surgical therapy; 2) had survived no more than 6 months since surgery; 3) Karnofsky performance status of at least 70% at study entry; 4) estimated life expectancy ≥ 6 months; and 5) aged between 18 and 65 years. All study subjects will meet all five inclusion criteria.

Exclusion criteria will be as follows: 1) subjects with serious systemic diseases, such as cerebrovascular, liver, kidney, hematopoietic system, and psychiatric diseases; 2) unable to participate in an exercise training because of either bone or joint diseases; 3) patients who are in other clinical trials; and 4) unable to understand Chinese. Every enrolled patient will sign an informed consent (seen in Additional file 2) before taking part in the later project procedures.

Measures to guarantee adequate participant enrolment will include: 1) a free rehabilitation and exercise training program; 2) the offer of priority access to specialist consultation; and 3) additional general guidance and disease consultation.

### Randomization and blinding

After completing baseline testing, each participant will be randomly allocated in a 1:1 ratio to either the TCC group or the placebo group. Each participant will learn of their group assignment by receiving a sequentially numbered and sealed opaque envelope from the project director and opening the envelope that contains the group assignment randomly assigned to their sequence number as randomly generated by the computer. Measurement technicians who are responsible for data collection and coding data are blinded to participant group assignment. In addition, all study personnel conducting the study assessments at baseline and postintervention will be blinded to treatment assignment for the duration of the study.

### Study interventions

Participants in each group will attend a supervised 1-h exercise session three times per week, starting 4 weeks after surgery at the earliest. A senior exercise physiologist will conduct the exercise session. Each session includes 10 min low-intensity warming up (50–60% of maximum heart rate) and 5 min cooling down at the beginning and end of the course, respectively. All interventions will be tailored to each participant following the principles of aerobic or resistance training prescription guidelines for adults as recommended by the American College of Sports Medicine (ACSM) [24]. The Borg rating of perceived exertion (RPE) and blood pressure will be assessed prior to and after the exercise, with heart rate and O_2_ saturation monitored continuously throughout.

#### TCC training

The TCC training group will learn to perform 24 standard TCC movements and breathing techniques taught by a professional TCC master with more than 20 years of teaching experience. The instructor explains the theory behind TCC and provides printed materials about TCC when the patient is placed in this group. In each session, participants practice TCC under the master’s instruction. Each session includes a 10-min warm-up about self-massage, breathing techniques, and relaxation in TCC, 45 min exercise training and 5 min cooling down. Throughout the intervention period, participants are required to practice TCC for 20 min every 4 days at home. After 3 months, participants are encouraged to practice TCC using an instructional DVD and keep record of activities until the follow-up visit at month 12.

#### Placebo control

Participants in the placebo control group will attend a supervised stretching program of the same frequency, duration, and length as the TCC group. The stretching program will be prescribed according to ASCM guidelines for people aiming to increasing whole-body flexibility. Stretches will be performed from a seated position in order to minimize weight-bearing forces. The stretching will also be limited in duration to 45 min, alternating between lower and upper body muscle groups in combination with warm-up and cooling down under the supervision of a professional physiologist. Throughout the intervention period, participants will be asked to stretch for 20 min every 4 days at home. After 3 months, participants will be encouraged to do stretching until the follow-up visit at month 12 and keep a record.

### Adherence considerations

Participants will be encouraged to accomplish the routine exercise over the 3 months. Several strategies will be employed to maximize adherence including individualized attention at the intervention sessions and telephone calls following missed sessions. In addition, participants who miss a session will be asked to attend a make-up class. Furthermore, we set the same classes in the morning and afternoon for patients to choose from, which promotes attendance by improving accessibility. Thirdly, all the participants will be asked to complete daily logs about the amount of time they practiced TCC or stretches. Finally, the study staff will also meet on a weekly basis to review each participant’s adherence.

### Study endpoints and assessments

#### Primary endpoint

##### VO_2peak_

VO_2peak_ will be evaluated using a physician-supervised incremental cycle ergometer test with 12-lead electrocardiogram (ECG) monitoring (Mac® 5000, GE Healthcare) under the supervision of a physiologist blinded to the patient’s randomization group. According to prior studies by Jones et al. [25, 26], all the subjects will pedal at 20 W for 1 min, and increase by 5 W every minute until exhaustion or a symptom-limited VO_2peak_ is achieved. Exercise will be terminated if any ECG abnormalities are observed.

#### Secondary endpoints

The secondary endpoints of this trial will be the 6-min walk distance (6MWD), lung function, patient-reported outcomes, and immunity function.

##### 6MWD

6MWD is a useful measure of functional capacity, which has been widely used for postoperative evaluation and for measuring the response to therapeutic interventions for pulmonary disease. The test will be performed according to current guidelines [27] in a 30-m corridor. Patients will be instructed to walk at their fastest pace and cover the longest possible distance in 6 min; pauses are allowed if needed. Waiting at least 1 h before a second test, the highest 6MWD is reported. Measurement of peripheral oxygen saturation and heart rate will be performed before and immediately after the test. Participants were asked to rate their post-test dyspnea and fatigue level using the Borg scale (rate 6–20) [28], with a higher rating corresponding to higher dyspnea or fatigue level.

##### Lung function

Lung function was found to be significantly associated with postoperative mortality in NSCLC, especially the percentage of forced expiratory volume in 1 s (FEV1) [29, 30]. This parameter will be evaluated using a calibrated spirometer (Spirovit SP-2; Schiller, Swizerland). FEV1 and forced vital capacity (FVC) will be measured, and FEV1/FVC will be calculated and compared to reference values [31]. The patients will be measured three times and the best result will be recorded.

##### Patient-reported outcomes

Patient-reported outcomes will include HRQoL, fatigue, dyspnea, depression, and anxiety. The 42-item Functional Assessment of Cancer Therapy–Lung (FACT-L) scale, which contains four subscales for physical (seven items), functional (seven items), emotional (six items), and social/family (seven items) well-being, plus a lung cancer-specific subscale (15 items), will be used to assess patient symptoms and HRQoL [32]. The 13-item FACT—fatigue scale will be used as the assessment of fatigue [33]. The Cancer Dyspnea Scale (CDS), which has been demonstrated to be a valid and feasible scale for assessing cancer-related dyspnea among NSCLC patients [34, 35], will be used to evaluate dyspnea [36]. Finally, depression and anxiety will be assessed using the Self-rating Depression Scale (SDS) and the Self-rating Anxiety Scale (SAS). All the above instruments have been found to be easy to administer, widely used, and reliable in prior research in lung cancer patients.

##### Immunity function

Immunity function will be tested by using peripheral blood samples collected at 7:00 am at baseline, at completion of the 3-month study, and at 9 months follow-up. Flow cytometry (Beckman Coulter EPICS XL; Beckman Coulter, Inc., Brea, CA, USA) will be used for the analysis within 24 h of collection of the blood samples. The percentage of T lymphocytes, CD4^+^ and CD8^+^ T lymphocytes, and the ratio of T helper/T suppresser cells will be used for the assessment.

### Tracking and monitoring of adverse events

Several methods will be used to assure the tracking and monitoring of adverse events: 1) all patients will be under the supervision of an oncologist and every single adverse event will be recorded on a case report form (CRF); 2) at the beginning of the training intervention, the physiologist will discuss the potential side-effects of the exercise, and all episodes occuring during the class will be recorded on the CRF; 3) during the exercise course and assessment, the blood pressure, heart rate, and SpO_2_ will be monitored in case of any negative side-effect; 4) any severe adverse event will be reported to the monitor of the trial and Guang’an Men Hospital within 24 h.

The time schedule of the study, including enrollment, interventions, assessments, and visits for participants, is shown in Fig. 2.

**Fig. 2 Fig2:**
[figure not shown]
Time schedule of enrollment, interventions, and assessments, as well as visits for participants. *6MWT* 6-min walk test, *CD* cluster of differentiation, *CDS* Cancer Dyspnea Scale, *ECG* electrocardiograph, *FACT* Functional Assessment of Cancer Therapy, *FEV1* forced expiratory volume in 1 s, *FVC* forced vital capacity, *NCI* National Cancer Institute, *PEF* parameter peak flow, *SAS* Self-rating Anxiety Scale, *SDS* Self-rating Depression Scale, *VO*_*2peak*_ peak oxygen consumption

### Data management and monitoring

A specialized clinical research associate (CRA) will be responsible for checking the ranges for data values. Double data entry will be conducted to promote data quality. Operations and data will be audited at the end of the trial by the state administration of traditional Chinese medicine, which is the department that oversees the project. Clinical Research Organizations (CRO), which are independent from investigators and the sponsor, will monitor the data during every participant visit.

### Statistical analysis

This randomized trial will recruit 120 subjects with postsurgical NSCLC. Unpaired *t* tests will be used to analysis the primary and secondary endpoints by comparing the TCC to the placebo group regarding mean improvement. We assume that improvement in VO_2peak_ in the TCC group will be 22.5%, while it will be 5% in the placebo group, as reported previously [15]; thus, a minimum of 55 patients per group will be required. Accounting for a 10% dropout rate, the inclusion of 60 patients per group results in a total of 120 patients.

The principal analysis of the study endpoints will employ the intention-to-treat (ITT) approach. The ITT analysis will include all randomized participants in the random allocation. The intervention group assignment will not be altered based on the participants’ adherence to the randomly allocated study arm. Patients who are lost to follow-up will be included in all primary and secondary analyses by assuming zero change across time. For the primary analysis, a multiple regression model will be used to regress change in VO_2peak_ on study group, the baseline value of the endpoint, and other pertinent baseline variables that may influence change in the study endpoints (e.g., co-morbid conditions/medications, self-reported exercise history, age).

All statistical analysis will be conducted using SPSS 17.0 statistics software. The data of all the endpoints are quantitative data. The mean ± standard deviation will be used to describe symmetric data validated by distribution pattern and homogeneity of variance, otherwise the interquartile range (IQR) will be used. If the data are symmetric after being validated by distribution pattern and homogeneity of variance, a *t* test will be used to compare the differences between the quantitative indices between the groups, otherwise the Wilcoxon rank-sum test will be used. For each endpoint, the overall alpha level will be controlled at a one-sided 0.05 by using Holm’s procedure [37]. The collected data will be examined, and the researchers will be supervised to control bias.

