The main outcome of the present trial is exercise capacity. The gold standard for measurement of exercise capacity is a direct measure of VO_2Peak_; other testing methods include the 6MWD, shuttle walk test, and stair-climbing test. Among these, VO_2peak_ and 6MWD are the two most frequently used (52% and 16%) [44]. Furthermore, VO_2Peak_ is an independent predictor of all-cause pulmonary morbidity [45, 46]. Brunelli and colleagues found that a VO_2Peak_ of no less than 20 mL/kg/min is a safe cutoff value, and no mortality was observed above this threshold for major lung resection [47]. Consistent with this, the findings of Jones et al. suggest that higher VO_2peak_ was associated with a statistically significant 21% to 24% reduction in the risk of mortality, and a VO_2peak_ of < 14 mL/kg/min may identify patients with poor prognosis [48]. Together, this indicates that VO_2peak_ is an emerging evaluating parameter of exercise training in patients with NSCLC. Specifically, research has shown TCC to be beneficial to the VO_2peak_ of middle-aged subjects [49, 50]. Despite the wealth of evidence, research has seldom explored the efficacy of TCC against exercise capacity or VO_2peak_. Thus, the primary outcome of this trial will be VO2peak. 6MWD and lung function will be set as simple and alternative elements to comprehensively assess the exercise capacity of this specific population.

Patients with operable NSCLC also experience fatigue and dyspnea, and are at risk for developing psychosocial problems, reduced quality of life as well as immune function. And, existing evidence have suggested that TCC has a promising function on enhancing proliferative and cytolytic activities of peripheral blood mononuclear cells (PBMCs), as well as increasing the ratio of T helper/T suppressor cells and mediating Th1/Th2 T-helper cell balance in postsurgical NSCLC patients, thus improving the immunity function of the patients [51, 52]. Therefore, our study also takes above symptom and immunity parameters into consideration to comprehensively evaluate the clinical benefit of TCC as an exercise intervention.

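### The primary analysis of VO2peak is stated in conflicting ways: an unadjusted t test in one paragraph, a baseline-adjusted regression in the next, and a general t test or Wilcoxon rule after that

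*Protocol article*

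**What the plan says.** VO2peak is the only primary endpoint. The Primary endpoint section names it, and the Discussion repeats this: "Thus, the primary outcome of this trial will be VO2peak".

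The Statistical analysis section then makes three statements that each reach this endpoint.

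- First paragraph: unpaired t "tests will be used to analysis the primary and secondary endpoints by comparing the TCC to the placebo group regarding mean improvement". The sample-size assumption follows directly, as an improvement of 22.5% against 5%.
- Second paragraph: "For the primary analysis, a multiple regression model will be used to regress change in" VO2peak on study group, the baseline value, and "other pertinent baseline variables that may influence change in the study endpoints". The further variables (comorbidity or medications, exercise history, age) are introduced as examples.
- Third paragraph: "The data of all the endpoints are quantitative data". A t test applies under the condition "If the data are symmetric after being validated by distribution pattern and homogeneity of variance"; "otherwise the Wilcoxon rank-sum test will be used". No test or cut-off is given for the check.

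The section also controls alpha for each endpoint at a one-sided 0.05 with Holm's procedure, without saying which tests form the family.

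**The concern.** A confirmatory trial needs one p value and one estimate named in advance for its primary endpoint. Here the first paragraph gives that role to an unadjusted t test and the second gives it to an adjusted regression. Two analysts following the text in good faith could report different primary results, and on borderline data one could be significant and the other not.

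Two things are at stake. If the choice is made once results are visible, the error rate exceeds the planned 5%. If the t test is reported, the trial gives up the baseline adjustment that its own second paragraph calls for, and with it some precision.

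This is more than detail left to an analysis plan. The article states two analyses for one role. A separate plan might choose between them, but the published text would still contradict itself.

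**Working it through.** **1. The statements side by side**

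| Paragraph | Analysis | Reaches VO2peak because | Status given |
|---|---|---|---|
| 1 | Unpaired t test on mean improvement | It names the primary endpoint | None beyond the assignment |
| 2 | Regression on group, baseline value and further covariates | It names VO2peak | Called the primary analysis |
| 3 | t test, or Wilcoxon if the checks fail | It calls all endpoints quantitative | General rule, conditional switch |

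Paragraphs 1 and 2 conflict directly. Paragraph 3 is consistent with paragraph 1, apart from the switch, and does not mention the regression.

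The sample size does not settle the matter. The 55 per group is stated without a standard deviation or power, so it cannot be reproduced or traced to either analysis.

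**2. Error rate if the more favourable result is reported**

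From the article: 60 per arm, one-sided 0.05, 10% dropout, and zero change assumed for patients lost to follow-up. Assumed here: no group effect, normal data, and a baseline to follow-up correlation r of 0.5 or 0.7. For each simulated trial, count a false positive if the smallest p value among the analyses considered is below 0.05.

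| Analyses considered (8,000 runs per r, no dropout) | r = 0.5 | r = 0.7 |
|---|---|---|
| t test or baseline-adjusted regression | 7.1% | 6.8% |
| t test, Wilcoxon or baseline-adjusted regression | 7.7% | 7.5% |

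Any one of these analyses, fixed in advance, stays near the nominal level (4.7 to 5.0%). With 10% of patients set to zero change, the better of t test and regression gives about 6 to 7%, and the best of all three about 7 to 8%.

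The second row treats Wilcoxon as a free choice. If paragraph 3 is instead applied as a rule, with an assumed 5% Shapiro/Levene trigger, the t test or Wilcoxon rule alone gives 5.2%. The better of that rule and the regression gives 7.1% (r = 0.5) and 6.9% (r = 0.7). Nearly all the excess therefore comes from the conflict between t test and regression.

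**3. Precision lost by reporting the t test**

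With equal variance σ² at both times:

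- variance of the change score: 2σ²(1 − r)
- residual variance after baseline adjustment: σ²(1 − r²)
- ratio: (1 − r²) / [2(1 − r)] = (1 + r)/2

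At r = 0.5 the ratio is 1.5/2 = 0.75, so the adjusted variance is 25% smaller. At r = 0.7 it is 1.7/2 = 0.85, or 15% smaller. This ignores the zero-change rule and any gain from further covariates.

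**4. The open covariate list (secondary)**

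A separate simulation assumed a change to baseline correlation of −0.3 or −0.5, three covariates each with coefficient 0.2, normal or skewed errors, and 10% set to zero change. The best of t test, Wilcoxon and full regression gave 7.5 to 8.8%. Free choice among the three covariates raised this to 8.7 to 10.8%. The covariate strengths are invented for illustration, so this shows direction only.

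**The case against.** The best defence is that the text does contain a ranking. Only the regression is introduced as the primary analysis, and only it names VO2peak as its outcome. The t-test sentence stands next to the sample-size assumption and may just describe the basis of that calculation. Paragraph 3 may be a general rule for the other endpoints. This is a fair reading and probably the intended one. But it requires the reader to set aside an express assignment of the primary endpoint to t tests, and a later rule whose opening covers all endpoints. The contradiction stands, though it is easy to resolve.

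Other parts of the defence succeed and limit the point. A reader might infer the following, which the article does not support:

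- *Three equal candidates.* Wilcoxon replaces the t test only when the distribution checks fail. Some latitude remains because the checks are undefined, but the main conflict is between two analyses.
- *A fourth test, on percentage change.* Percentages appear only in the sample-size assumption, and no sentence names such a test. The scale of the improvement or change is left unstated, which needs a word in the fix but adds no listed analysis.
- *Different treatment effects.* Under randomisation the change-score t test and the baseline-adjusted regression target the same mean difference on the same scale. They differ in precision. Only Wilcoxon addresses something else.
- *An open model as a major fault in itself.* The baseline value is fixed and three kinds of further covariate are named. Closing such a list is commonly left to an analysis plan, which is not shown.

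Holm's procedure might be thought to cover the choice of method. The text does not say so.

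**Conclusion.** The point holds as a stated contradiction over the primary analysis, chiefly between the unadjusted t test and the baseline-adjusted regression. Reporting the more favourable of the two would raise the one-sided error rate from 5% to about 6 to 7%, and to about 7 to 8% if Wilcoxon were also chosen freely. These rates describe what selective reporting would do. Nothing in the article suggests that the investigators intend it.

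The correlations of 0.5 to 0.7 are assumptions, and the precision figures also need equal variances at both times. The contradiction itself rests on neither. The error inflation is modest, but it affects the trial's one confirmatory result and costs little to remove.

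**What to change.** State that the single primary analysis is the regression of change in VO2peak from baseline to the end of the intervention (month 3), on one stated scale, on randomised group and baseline VO2peak. Fix any further covariates before unblinding, drawn from those the plan already names: comorbidity or medications, exercise history, and age. Month 3 follows the Abstract, which has all endpoints assessed at baseline and postintervention. Because the Abstract also lists months 6, 9 and 12 as main time points, the sponsor should confirm it.

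Remove the primary endpoint from the t-test sentence in the first paragraph. In the third, label the t test and Wilcoxon comparisons of VO2peak as supportive analyses that cannot replace the regression.

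The cost is wording, provided that the data are still blinded and that the named covariates were recorded at entry. The article confirms neither. Trial status says that all 120 patients have been recruited and that the study ends in 2017, so the change should be made and dated promptly. If unblinding has already happened, the report should give both the t test and the regression and say that the plan did not rank them clearly.

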## Trial status

The study will end in 2017. To date, all 120 patients have been recruited.

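### Sixty per group covers 8.3% dropout, not the stated 10%: a minor arithmetic error in the sample-size justification

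*Protocol article*

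**What the plan says.** All the figures are in the Statistical analysis section of the protocol article. The assumed effect is "improvement in VO_2peak_ in the TCC group will be 22.5%, while it will be 5% in the placebo group", a difference of 17.5 percentage points. From this the article concludes "thus, a minimum of 55 patients per group will be required", and the next sentence reads "Accounting for a 10% dropout rate, the inclusion of 60 patients per group results in a total of 120 patients".

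The following paragraph fixes the analysis set: "The ITT analysis will include all randomized participants in the random allocation". Patients lost to follow-up stay in every primary and secondary analysis, with their change set to zero. The last paragraph of the section says "the overall alpha level will be controlled at a one-sided 0.05", but does not tie that level to the sample-size calculation. Neither the power nor the SD behind the 55 is given.

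Allocation is 1:1 (Randomization and blinding), and Trial status reports "To date, all 120 patients have been recruited".

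**The concern.** The minimum, the dropout rate and the enrolled number stand in two adjacent sentences, and any two of them contradict the third. The number enrolled does not leave the stated minimum once the stated loss has occurred. This is not a detail that an article leaves to a fuller document, because all three figures are given.

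The sentence also treats dropout as a loss of patients from the analysis, whereas the next paragraph keeps those patients in with zero change. Under that rule dropout acts mainly by shrinking the expected difference, which the dropout allowance does not mention.

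At stake is the accuracy of the published size justification. Neither the conduct of the trial nor the validity of its test is affected.

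**Working it through.** **Inputs from the article (Statistical analysis):** minimum 55 per group; dropout 10%; 60 per group enrolled; mean improvement 22.5% against 5%; alpha 0.05 one-sided; zero change for patients lost.

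**Assumed, because the article is silent:** 55 per group gives 80% or 90% power; equal SD in both arms; 10% loss in each arm; an unadjusted comparison of means. One-sided and two-sided 0.05 are both shown, since the level used for sizing is not stated.

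**1. The dropout allowance**
- Completers at 10% loss: 60 × 0.90 = 54, which is below 55.
- Loss that 60 can absorb: (60 − 55)/60 = 5/60 = 8.3%.
- Enrolment needed for 55 completers: 55/(1 − 0.10) = 61.1, rounded up to 62 per group (124 in total).
- Multiplying instead of dividing: 55 × 1.10 = 60.5, rounded up to 61.

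*Can 60 be reproduced?* Not exactly from 55 by either route with rounding up, although it is within 2 patients of both. If 55 is itself a rounded-up figure, an unrounded value above 54 and up to 54.54 times 1.10 gives 60 or less (54.54 × 1.10 = 59.99). The multiplicative shortcut could therefore have produced 60. Division could not: 54/0.90 is exactly 60, so any value above 54 gives more than 60.

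**2. Power with 54 completers**

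The SD is back-solved so that n = 55 gives the assumed power:

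SD = 17.5 × √(55/2) / (z for alpha + z for power)

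For one-sided 0.05 and 80%: 17.5 × 5.244 / (1.645 + 0.842) = 36.9 points.

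Power at 54 = Φ(17.5 / (SD × √(2/54)) − z for alpha) = Φ(2.464 − 1.645) = 79.4%.

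**3. Power under the plan's zero-change rule**

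All 60 per group are analysed. With 10% of each arm set to zero, the expected means are 0.9 × 22.5 = 20.25 and 0.9 × 5 = 4.5, a difference of 15.75 points.

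- *SD unchanged:* Φ(15.75 / (36.91 × √(2/60)) − 1.645) = Φ(2.337 − 1.645) = 75.6%.
- *Variance effect of the zeros included:* the variance in each arm is 0.9 × SD² + 0.09 × mean². For TCC this is 0.9 × 36.91² + 0.09 × 22.5² = 1271.5; for control, 0.9 × 36.91² + 0.09 × 5² = 1228.2. The standard error is √((1271.5 + 1228.2)/60) = 6.455, so power is Φ(2.440 − 1.645) = 78.7%.

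The same formulas for each assumption (normal approximation):

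| Assumed power at n = 55 | Sidedness | Implied SD | 60, no loss | 54 completers | 60, zeros, variance effect included | 60, zeros, SD unchanged |
|---|---|---|---|---|---|---|
| 80% | one | 36.9 | 83.0% | 79.4% | 78.7% | 75.6% |
| 80% | two | 32.8 | 83.3% | 79.3% | 78.3% | 75.0% |
| 90% | one | 31.4 | 92.1% | 89.5% | 88.8% | 86.6% |
| 90% | two | 28.3 | 92.3% | 89.5% | 88.5% | 86.2% |

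Below the assumed design power, the completer shortfall costs about 0.5–0.7 point. The zero-change rule costs about 1–2 points with the variance effect included, or about 3–5 points with the SD unchanged.

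**The case against.** The strongest reply is that the discrepancy is one completer per group against a dropout rate that is itself a round planning guess. It costs less than one point of power, is within ordinary rounding, and could have come from a common shortcut applied to an unrounded sample size. All of that stands, and it is why the point is minor. It does not make the sentence correct, because 55 is presented as a minimum and the stated loss goes below it.

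A second reply is that the intention-to-treat rule keeps all 60 per group in the analysis, so the number analysed never falls to 54. This is right, and it rules out a stronger reading. A reader might infer that the trial drops below its own minimum once more than 5 patients per arm are lost. That would hold only if dropouts left the analysis, and the plan says that they do not. The reply does not rescue the allowance, however: under every assumption tabulated, 60 analysed with 10% zeros has slightly less power than 54 completers.

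A third reply is that no power figure can be attributed to the trial. This also stands. A reader might take 80% as the design power, but the article states neither a power nor an SD, so the percentages above show only the size of the effect.

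**Conclusion.** There is a minor arithmetic error in the stated dropout allowance. On the article's own numbers, 60 per group covers 8.3% loss and not 10%; this part needs no assumption.

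The power consequences rest on an assumed design power of 80% or 90% at n = 55, the SD implied by it, and equal loss in both arms. On that basis 54 completers give about 79.3% or 89.5%. The zero-change rule gives about 78–79% or 88.5–89% with the variance effect of the zeros included, and about 75–76% or 86–87% with the SD unchanged. Dilution of the difference from 17.5 to 15.75 points therefore matters somewhat more than the missing completer, and inflating enrolment for dropout does not describe it.

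The documents do not support a claim that the trial is materially underpowered for this reason. Whether 55 is itself adequate cannot be checked from what is stated.

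**What to change.** Enrol no more patients, since recruitment is complete. Replace the dropout sentence with wording such as:

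*Sixty patients per group keeps 55 completers with up to 8.3% loss (5 of 60); at 10% loss, 54 per group complete. All 60 per group are analysed, with zero change for those lost, so 10% loss in each arm reduces the expected difference from 17.5 to 15.75 percentage points.*

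If a power figure is added, state next to it the SD, the design power and the sidedness on which it rests. Without them no figure can be checked.

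The cost is a sentence or two of text and a stated dropout tolerance of 8.3% in place of 10%. Enrolment, conduct and analysis do not change.
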